**Background**

Problematic alcohol use is today the third largest cause of disease worldwide and one of the greatest challenges to public health, causing death and disability worldwide (WHO, 2009). From a global perspective, almost four per cent of all deaths worldwide are attributable to alcohol, which is more than, for example HIV / AIDS, violence or tuberculosis. Consumption of alcohol is regarded as the direct cause of 60 different types of diseases and injuries, and indirect cause to another 200. In Sweden alcohol consumption has increased since the mid-1990s. Although some decline has been seen in recent years, according to SoRAD estimates, consumption, is still almost 20 percent higher today than in the mid-1990s (H. Leifman & Ramstedt, Preliminary version 2009-11-11). In The Abuse commission's final report "Better response to abuse and dependence" (SOU 2011: 35, 2011) the investigator estimates that about 700 000 people in Sweden have a harmful use of alcohol and that 330 000 of these have an alcohol dependence. Regarding hazardous use of alcohol, a use not yet developed to harmful use or dependence, it is estimated that about a million Swedes have such hazardous use. In 2009, the Institute of Public Health reported that 18% of men and 10% of women had a hazardous alcohol use (Cleve Palm & Karlsson, 2009). Despite a relatively large part of the Swedish population having a problematic alcohol use, we know that most of them do not seek treatment (Blomqvist, Cunningham, Wallander, & Collins, 2007). A survey showed that only 18% of all the alcohol dependent people in the county had contact with the specialized addiction care (Andréasson, 2010). There seems to be a big group of people who need to change their drinking habits but who, for various reasons, do not come into contact with addiction care. In an opinion survey conducted on behalf of the National Institute of Public Health in 2009 78% of respondents stated that they would use the Internet to obtain information about alcohol and other drugs, and focus group interviews with risk consumers of alcohol has shown that the help people primarily want for their problematic use consists of reliable information, preferably in the form of web-based test. Studies on Swedish Internet-based self-test of problematic alcohol and drug use show that they are an effective way to reach both those with problematic use and groups less accessible to healthcare, such as women and young adults (Sinadinovic, Berman, Hasson & Wennberg, 2010; Sjölund, 2007).

In a comparison with the situation in the 1990s, alcohol consumption in Sweden has increased faster among women than among men (CAN, 2009) and a population screening in 2008 revealed no notable differences in the prevalence of problematic alcohol use between women and men, (a total of 20% of women and 22% of men had a problematic alcohol use). Problematic drug use was more common among women - 3.8% - than 1.8% among men (Sinadinovic, Wennberg, & Berman, 2011. The gender distribution within specialized addiction care in Stockholm County shows that only 33% of patients in 2010 were female and 67% male (A. Leifman, 2011). Similar figures are reported in the Netherlands (Postel, de Haan, best Huurne, Becker, & de Jong, 2011). This suggests that it is particularly difficult for addiction services to reach women with problematic use of alcohol and drugs. Meanwhile, earlier research has shown that women are particularly attracted to internet based interventions and that, when it comes to the use of such services, at least 50% are women (Koski-Jännes, Cunningham, Tolonen, and Botha, 2007; Postel et al., 2011; Sinadinovic, Berman et al., 2010). Delivering interventions for problematic alcohol and drug use over the Internet should be suitable for Swedish conditions where 85% of the Swedish population use the Internet: Sweden is one of the countries in the world where Internet use is highest and most widespread in society; additionally current Swedish research suggests that Internet-based interventions for problematic alcohol and drug use might appeal to users in the Swedish population (Sinadinovic, 2012). A Canadian study has also shown that the majority of people with problematic alcohol and/or drug use use the Internet, even to a greater extent than those without such problematic use (Cunningham, Selby, Kypri, & Humphreys, 2006).

To date, treatment for problematic alcohol use over the internet has been tested in Sweden only in self help format (without therapist support), where help seekers on the internet were randomly assigned to eScreen.se (screening site), alkoholhjalpen.se (self-help modules) or a control group that completed questionnaires; follow-up was done after 3, 6 and 12 months (Sinadinovic, Wennberg, Johansson, & Berman, 2012). Alkoholhjälpen.se yielded better effect for those who had a little less severe problems. Of those who used eScreen.se 70% went on to talk to someone about their problems, compared with 49% from Alkoholhjälpen and 56% for the control group. These results are consistent with the overall positive results of the studies included in the review articles and meta-analyzes (Newman, Szkodny, Llera, & Przeworski, 2010; Rooke, Thorsteinsson, Karpin, Copeland, & Allsop, 2010).

**Purpose**

The general purpose of the study is to perform a randomized pilot study testing a Swedish version of an existing Dutch e-health program, *Therapy Online (TO),* for the treatment of problematic alcohol use. The program has demonstrated good results in a randomized controlled study (Blankers, Koeter & Schippers, 2011).

Specific issues of the pilot study are three:

1. In previous research, our research team offered 1000 people, out of a random population sample, a choice between answering questions about alcohol and drug use via Interactive Voice Response (IVR, automated telephony) or the Internet. In the same study 2000 people were offered to answer questions via IVR, and an additional 2,000 people answered the questions via the Internet (web forms). It turned out that the group receiving a choice between IVR and the Internet participated to a significantly greater extent in the study of the response rate (Sinadinovic et al., 2011). In this study we want to examine whether the possibility to opt for email and instant messaging provides better retention in the study. In order to answer this question grup 1 ***consists of*** 20 individuals who get to choose *whether they* want to have contact with a therapist through synchronous chat sessions or asynchronous e-mail messages.
2. In the program developed by the Jellinek Clinic in Amsterdam (where the evaluation made by Blankers et al., 2011) seven 40-minute chat sessions in real time were delivered to participants. In Sweden, however, internet treatment with therapist support for patients with depression and anxiety diagnoses is given via asynchronous messages (internetpsykiatri.se in the Stockholm County Council). This delivery method is more flexible for both finishers treated, and also cheaper to the caregiver. We are interested in examining the extent to which it works to offer the TO with therapist support in the form of written messages (corresponding email). To answer this question ***group 2 will consist of 20*** individuals who are randomized to Therapy Online programwith therapist support in the form of asynchronous text messages.
3. The study published by Blankers et al. (2011) consisted of three arms: TO with therapist support in the form of seven 40-minute chat sessions in real time, TO without therapist support and a control group in the form of a waiting list. In this pilot study, we want to partially replicate Blankers et al. study and compare treatment outcomes for TO with therapist support, with the outcome of the TO without therapist support. In order to answer this question 40 individuals will be randomized into ***group 3 to receive*** TO without therapist support. Answering this question will be generated after the data analyzes where groups 1 and 2 will be compared with group 3.

**Design**

As stated above the study is a randomized, controlled pilot study [1] with three arms:

1. TO with therapist support, choice between synchronous chat or asynchronous messaging, *n* = 20
2. TO with therapist support, asynchronous *messages,* n = 20
3. *TO without therapist support = 40*

Measurement based questionnaires (see below) occurs at recruitment to the study (T1) and at the completion of the study 10 weeks after recruitment (T2). See Figure 1 for the flow chart.

**Materials**

*The treatment program TO*

The treatment used in this study is a Swedish translation of a Dutch program that has shown very good outcomes in a randomized controlled study, where the program was compared to a self-help variation without therapist support (Blankers et al., 2011). The program contains eight modules focusing on relapse prevention (Saxon & Wirbing, 2004).

*Figure 1.* Three-arm pilot study of Internet-based treatment for problematic alcohol use with and without dealing with support

*Outcome Measure*

AUDIT (Alcohol Use Disorders Identification Test) (Annex 5.1)   is a well established and widely used instrument for assessing alcohol consumption (Bergman & Källmén, 2002; Saunders, Aasland, Babor, De La Fuente, & Grant, 1993). It consists of 10 questions answered 0-4 with a final score between 0 and 40. The result is then divided into hazardous use, abuse and dependence. Limit the risk of abuse required for men at 8 points or more, for women at 6 points or more. There is also a short version of the instrument, the AUDIT-C ("consumption"), which contains only the first three questions and is used to map the current situation. On some occasions it may be expedient to use one single query to get a picture of someone's drinking. For these cases, question 3 concerning high episodic drinking is the one that is best correlated with the total score (Berman, Wennberg, & Källmén, 2012).

 DUDIT (Drug Use Disorders Identification Test) (Appendix 5.2)   is a questionnaire designed to find out drug consumption and drug-related problems of various kinds.   The test consists of 11 questions that are scored between 0 and 4, giving a final score of 44 points. The result of the test is divided into hazardous use, abuse and dependence. The test has been shown to identify problematic use in studies. As for the AUDIT, there is a shorter version of DUDIT, DUDIT C, where only the first four questions dealing with consumption included. This version of the test, however, is unfortunately not enough studied. What you can infer is that the limit of 1 point for hazardous use applies to both DUDIT C as well as for DUDIT. (Berman, Bergman, Palmstierna, & Schlyter, 2005; Berman et al., 2012).

TLFB (Timeline Follow Back) (Appendix 5.3) is an instrument for measuring the consumption of alcohol or drugs over time and has been used successfully in the periods up to 12 months back (Sobell & Sobell, 1992). There have also been attempts to use the method over a period of 24 months with mixed results (Day, Collins, Degenhardt, Thetford, & Maher, 2004). Sobell and Sobell (1992) generally suggest the help of a calendar chart during the time drinking should be assessed. Besides the calendar, you can use a written support to convert the amount of alcohol consumed to standard glass. Furthermore seeking man during the time period to identify so-called key dates (birthdays, holidays, weekends) and periods when drunk or abstention from alcohol. It then uses the key dates and periods as so-called anchor points to find out how much you drank then. One recommendation is to initially identify upper and lower limit for alcohol consumption during the period so that you know in which range you move. In the present study, we ask participants about their drinking during the last 7 days, as in the study conducted by Blankers et al. (2011). It is worth noting that no clear support existed for longer periods of study gives more reliable results.

RCQ (Readiness to Change Questionnaire) (Appendix 5.4) is a test developed to measure the motivation to change (Forsberg, Ekman, Halldin, & Rönnberg, 2004; Role Nick, Heather, Gold, & Hall, 1992). The test consists of 12 questions and follow DiClemente and Prochaska model of "stages of change" which describes the process when a person tries to solve its problems of dependence (Prochaska & DiClemente, 1986). In a recently published doctoral thesis psychiatric patients who changed their drinking habits after a short intervention from the beginning changed their habits to a greater extent than those who did not receive an intervention (Gordh, 2012). Questions have been raised about RCQs ability to predict outcomes (Forsberg et al., 2004).

VAS measures of motivation (Readiness Ruler) (Appendix 5. 4.1) consists of a scale where the respondent on a line places its response between two answers, in this case the statement *"I'm not ready to change my drinking habits" and "I'm very much ready to change my drinking habits."* High performance on the scale, especially in the upper tertiary, correlates with lower levels of drinking during follow-up after three months (Bertholet, Cheng Palfai, Samet, & Saitz 2009).

WHOQOL-BREF (Appendix 5.5) is a test to assess quality of life developed by the World Health Organisation. It consists of 26 questions that are scored from 1 to 5. The test is a short version of a longer WHOQOL-100. WHOQOL-BREF correlates strongly with WHOQOL-100 on all dimensions excluding that social (O'Carroll, Smith, Couston, Cossar, & Hayes, 2000). The test has been used in extensive research since it was introduced and keeps good cultural validity (Skevington, Lotfy, & O'Connell, 2004).

EQ-5D -5 L (Appendix 5.6) is an assessment instrument for quality of life that consists of 5 questions with five possible answers each. The test also includes a Visual Analogue Scale (VAS) to ask where the respondent is invited to mark their health on a graduated line from 0 to 100 (Rabin & Charro, 2001). The test is available in two editions: first, the EQ-5D 3L where each question has three possible answers per question, and the EQ-5D-5L with five answer options per question. In recent years evidering retained the five dimensions but all of a response alternatives were expanded from three to five (Herdman et al., 2011). This instrument has been used in various clinical populations and may be less sensitive to the quality of life in non-clinical populations (the Willige, Wiersma, Nienhuis, and Jenner, 2005), consequently the EQ-5D 5L and WHOQOL-BREF used in this study.

HADS (Hospital Anxiety and Depression Scale) (Appendix 5.7) is a questionnaire commonly used in health care to identify anxiety and depression. The form consists of a total of 14 questions, seven for anxiety and depression each, and scored 0-3. Maximum points for anxiety and depression is 21 and a result of 15 points or more suggests that further treatment measures should be initiated. The tool has in studies been compared to BDI (The Beck Depression Inventory) and STAI (Stait-Trait Anxiety Inventory) and has shown good psychometric properties, both with respect to the correlation with the BDI and STAI, to internal consistency and stability, and in test-retest (Michopoulos et al. , 2008).

SRS (Session Rating Scale) (Appendix 5.8.1 for group 1 & 2 and 5.8.2 for Group 3) is a tool to measure the alliance. It can be administered after each session or module. It is a short test where the respondent is asked to consider the extent to which he or she agrees with four different statements; *"I* felt *heard, understood and respected." "We worked with or talked about it that I wanted to work with and talk about."* " *The way we worked in suits me fine.* "And" *Today's talks suited me perfectly.* ". Grading is done on a VAS-scale (Visual Analogue Scale) with the above statements on the one hand and the claims formulated as negatives of the other. SRS is clearly analogous to the longer test designed to measure the same thing, both in terms of validity and reliability (Campbell & Hemsley, 2009).

Follow-up questions (Appendix 5.9.1 Group 1 & 2 and 5.9.2 of Group 3) will investigate how participants experienced the Internet treatment; if they missed having telephone or physical contact, if they experienced the treatment as effective and whether they would recommend the treatment to anyone. The answers are sometimes graded, sometimes formulated as "Yes," no "and" do not know " (Postel et al, 2011).

  Other forms of treatment (Appendix 5.10)  This short questionnaire developed by the research group contains three questions relating to whether the participant used other measures of help besides the Internet treatment to manage his or her problem, including questions about medication and whether the person had contact with other responders - both self-help, telephone or customary care. By controlling for other factors, it becomes easier to assess the impact of the completed treatment (Sinadinovic et al, 2012; Sinadinovic, Johansson, Wennberg, & Berman, 2010).

**Participants**

A total of 80 people seeking help via the Internet will be recruited (see below for the recruitment procedure). All information and informed consent will be done on the Internet-based platform in line with previous studies that we have conducted. Individuals who are 18 years or older with at least risky use of alcohol (≥6 p for women and ≥ 8 p for men) on the AUDIT included in the study. Furthermore, we will inform the participants that it is important that they intend to be available via the Internet for study within the next 10 weeks of the study. Persons under 18 and / or without risky use of alcohol are excluded. Persons who receive over 15 on the estimates of anxiety and depression the HADS, those who get a result that is two standard deviations or more below average in any of the instruments that measure quality of life (WHOQOL-BREF and the EQ-5D) may participate in the study but are recommended after 10 weeks to seek psychiatric help. Participants at the end of the study, scoring higher than 20 on the AUDIT will receive a recommendation to turn to specialized addiction treatment or addiction treatment provided by social services. Participants who, according to the Drug Use Disorders Identification Test (DUDIT), have an active drug use in parallel with the use of alcohol will be allowed to participate in the study, but if continuing drug use at the end of the study, they will receive a recommendation to above apply to the specialized addiction care or social services to continue help. Personal advice on this can be given if the person contacts the research team. Contact details will be available when logging on the personal user account, the treatment site. We expect that a smaller proportion of participants in the study will show signs of problematic drug use in parallel with problematic alcohol use. One population survey of drug problems from 2008, where DUDIT questionnaire was used, shows that the risk of drug consumption in 2% of the Swedish population and the harmful use of 2.8% (Sinadinovic et al., 2011).

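### The protocol's HADS referral rule starts above 15, but its own description of the HADS puts the limit for further measures at 15 or more, so a score of exactly 15 triggers no HADS-based recommendation

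*Protocol*

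**What the plan says.** The protocol states a HADS limit in two places.

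- **Materials, Outcome Measure (HADS).** The instrument is described so: "The form consists of a total of 14 questions, seven for anxiety and depression each, and scored 0-3", with a maximum of 21 for each of anxiety and depression. On interpretation, "a result of 15 points or more suggests that further treatment measures should be initiated".
- **Participants.** The operative rule covers "Persons who receive over 15 on the estimates of anxiety and depression the HADS". The same sentence adds a second trigger, "a result that is two standard deviations or more below average in any of the instruments that measure quality of life". People who meet either one "may participate in the study but are recommended after 10 weeks to seek psychiatric help".

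No other section gives a HADS cut-off or links a HADS score to an action.

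**The concern.** The same number is used with two different boundaries. The instrument description includes 15 in the range that calls for further measures; the rule that staff or the platform would apply leaves it out. No reason is given for acting one point later than the description suggests.

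At stake is a recommendation to seek psychiatric help. Applied literally, the rule gives a participant with exactly 15 no recommendation on the HADS result, although the protocol itself flags that score. Because this is a rule for participant care that the protocol fixes in its own text, it is not a detail left for a statistical analysis plan. No estimate, test or sample size depends on it.

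**Working it through.** **1. The two rules on the HADS scale**

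Inputs, all from the HADS description in Materials: seven items per subscale, each scored 0 to 3.

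- Subscale maximum: 7 × 3 = 21, which agrees with the stated maximum.
- Scores are sums of whole numbers, so *over 15* means 16 or more.
- Limit in Materials (15 or more): scores 15 to 21, that is 21 − 15 + 1 = 7 values.
- Limit in Participants (over 15): scores 16 to 21, that is 21 − 16 + 1 = 6 values.
- Difference: the single score 15.

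The protocol does not say whether the limit applies to each subscale or to the 14-item total. The conflict at 15 is the same either way, because the total is also a whole number.

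**2. Whether another rule closes the gap**

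| Route | Section | Tied to a HADS score of 15? |
|---|---|---|
| Quality of life two standard deviations or more below average | Participants | No |
| Contact with a licensed therapist if mood worsens considerably, so that treatment cannot or should not continue | Procedure, Treatment | No |
| Weekly therapist support (groups 1 and 2) | Procedure, Treatment | No |
| Questions to the research team (group 3) | Procedure, Treatment | No |

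Each may reach some participants who score 15. None would do so because of that score.

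**3. How many participants might score exactly 15**

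The protocol gives no HADS mean or standard deviation, so this step rests on assumption. Take a subscale score as normal, rounded to whole points and truncated to 0–21, with mean m and standard deviation s:

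P(15) = [Φ((15.5 − m)/s) − Φ((14.5 − m)/s)] / [Φ((21.5 − m)/s) − Φ((−0.5 − m)/s)]

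P(15 or more) has the same denominator, with numerator Φ((21.5 − m)/s) − Φ((14.5 − m)/s). Expected counts are 80 times these probabilities, 80 being the planned sample.

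| Assumed mean, SD | P(15) | P(15 or more) | Share at exactly 15 | Expected at 15, of 80 | Expected at 15 or more, of 80 |
|---|---|---|---|---|---|
| 6, 3 | 0.0016 | 0.0023 | 67% | 0.1 | 0.2 |
| 6, 5 | 0.0176 | 0.0483 | 36% | 1.4 | 3.9 |
| 8, 4 | 0.0221 | 0.0526 | 42% | 1.8 | 4.2 |
| 10, 4 | 0.0460 | 0.1291 | 36% | 3.7 | 10.3 |
| 10, 5 | 0.0498 | 0.1784 | 28% | 4.0 | 14.3 |

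A beta-binomial on 0–21 with the same range of means and standard deviations gives 0.2 to 4.1 of 80 at exactly 15, and shares of 24% to 60%. Both shapes therefore put the count at roughly 0 to 4 of 80 per subscale per assessment.

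**The case against.** **The two sections do different jobs.** Materials describes the instrument in general terms; Participants sets the study procedure. A study may choose to act one point above a guide value, and staff have only one operative rule to follow. It is true that conduct is not ambiguous. But the protocol states no choice of a stricter limit, and the result is that it takes no HADS-based action at a score it has itself flagged.

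**Translation.** The text reads as a translation from Swedish and the phrase in question is garbled, so *over 15* may be loose wording for *15 or more*. This is plausible, and a deliberate shift of the boundary is not shown. If it is the explanation, the correction restores what was meant.

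**Is the HADS limit a lone anomaly?** A reader might infer so, because the AUDIT entry limits agree between Materials ("Limit the risk of abuse required for men at 8 points or more, for women at 6 points or more") and Participants ("≥6 p for women and ≥ 8 p for men) on the AUDIT"), and the quality-of-life trigger is inclusive. The protocol does not support that pattern. The recommendation for specialised addiction care at the end of the study is also worded exclusively, for AUDIT scores above 20. That limit has no inclusive counterpart in Materials to contradict, so the HADS conflict stands on its own two statements and not on a pattern across instruments.

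**Is a participant at 15 cut off from help?** A reader might infer this too, and it goes too far. The quality-of-life trigger and the support routes listed in the working remain open. They lessen the consequence without removing the mismatch.

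**Conclusion.** The protocol is inconsistent as written: Materials includes a HADS score of 15 in the range that suggests further measures, and the only HADS-based action, in Participants, excludes it. This is certain from the text and needs no assumption beyond whole-number scoring. Severity is minor. Eligibility, randomisation, outcomes and analysis are untouched.

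The size is not known. The figure of roughly 0 to 4 of 80 rests wholly on the assumed means, standard deviations and distribution shapes. It should not be read as an upper bound on participants affected: it counts one subscale at one assessment, a participant could score 15 on either subscale, and the beta-binomial already goes slightly above the highest normal value (4.1 against 4.0). In the other direction, some of those counted would receive the recommendation through the other subscale or the quality-of-life limit. Nor are the shares at exactly 15 evidence from this trial; they follow from the assumed tails.

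**What to change.** In the HADS rule under Participants, replace *over 15* with *15 or more*, to match the HADS description under Materials. In the same edit it would help to say that the limit applies to either subscale. The timing of the recommendation, at 10 weeks, stays as it is.

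The cost is one phrase and at most a few more recommendations at 10 weeks. If the higher limit was intended, the alternative is a sentence in Participants that says so and gives the reason.
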